## Abstract

**Background::**

As a common and frequent disease in pediatric patients, pediatric anorexia (PN) poses a serious threat to childhood growth and health. In recent years, societal changes in lifestyle and diet have increased the incidence of this PN, which has attracted extensive attention from both the medical community and parents. It has been shown that massage therapy represents an effective intervention for the treatment of anorexia, but investigation on its mechanism(s) of action remains limited. In this study, we will explore the biological mechanism(s) of PN from the perspective of intestinal flora, to further reveal its site of action and therapeutic mechanism(s).

**Methods::**

A total of 60 healthy children will be randomly selected for physical examination. According to a random number generated by a computer, children with anorexia who meet the inclusion criteria will be selected. In strict accordance with the time sequence of inclusion, subjects will be randomly assigned to either the massage or control group (n = 60 per group). The blank group will receive no treatment. Children in the massage group will receive a designated massage protocol. The control group will be administered oral Jianweixiaoshi tablets over 4 weeks. Each group will be compared for intestinal flora structure, fecal short chain fatty acids levels, serum trace elements, urine D-xylose-excretion rates, gastric fluid emptying, gastric motility, and hemoglobin levels before and after treatment.

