#### Statistical analysis

2.11.6

SPSS22.0 statistical software will be used for all analysis. Data will be graded using rank sum tests. *χ*^2^ tests will be used for data counts. Measurement data will be shown as the mean ± standard deviation. Data with a normal distribution will be analyzed using a 1-way analysis of variance. Least Significant Difference tests will be adopted for parity of variance. A Games–Howell test will be adopted for data with a non-normal distribution. The rank sum test was used for those who did not conform to normal distribution. *P* < .05 will be considered statistically significant.

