## Limitations of the study

5

1.The control group drug will receive a widely used clinical drug that is recommended by Chinese guidelines. Its safety and efficacy have been proven through years of clinical application, but it is not currently recommended in relevant international guidelines.2.All subjects are of the same ethnicity. Whether massage therapy is effective for other ethnicities/regions requires confirmation in future multi-center and large-sample trials.3.Intestinal flora are susceptible to a variety of factors, particularly dietary factors.^[23]^ It is therefore difficult to exclude the influence of diet on the digestive tracts of the children. This study will provide dietary and water guidance, providing suggestions to minimize the bias in the final results.

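### Main and secondary outcomes are compared before and after treatment, but the stated tests have no baseline covariate and the analysed variable (final value or change) is not named, so precision is given up on either reading

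*Protocol article*

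**What the plan says.** The Abstract (Methods) lists flora structure, fecal short chain fatty acids, serum trace elements, urinary D-xylose excretion, and then "gastric fluid emptying, gastric motility, and hemoglobin levels before and after treatment". These are all the main and secondary outcomes of section 2.11; adverse events are handled separately. The two randomised arms, massage and tablets, have 60 children each. The third group is 60 healthy children who are not randomised against them. The tablets run for 4 weeks: "The control group will be administered oral Jianweixiaoshi tablets over 4 weeks".

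Section 2.11.6 assigns tests by type of data. For measurement data: "Data with a normal distribution will be analyzed using a 1-way analysis of variance". Pairwise follow-up is by LSD ("Least Significant Difference tests will be adopted for parity of variance") or Games-Howell ("A Games–Howell test will be adopted for data with a non-normal distribution"), and there is a rank sum option: "The rank sum test was used for those who did not conform to normal distribution". Counts get chi-square tests, and significance is at 5%.

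The section names no baseline covariate, change score, paired test, repeated-measures model or group-by-time term. It does not say which value enters the ANOVA or the rank sum test.

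**The concern.** The design yields two values per child for each outcome, and the tests named do not model the first when comparing the second. A one-way ANOVA has group as its only factor. Its input could be the post-treatment value, which leaves the baseline out, or the change, which subtracts the whole baseline whatever its correlation with follow-up. Neither uses the baseline as efficiently as adjusting for it.

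What is at stake is precision in a trial of fixed size, and clarity about which comparison carries the conclusion. The Abstract's wording can be read as comparing each group with itself over time. A change within the massage arm would also contain natural recovery, regression to the mean and any effect of dietary advice. Section 5 says that flora is sensitive to diet and adds: "This study will provide dietary and water guidance, providing suggestions to minimize the bias in the final results". Only the contrast between the randomised arms separates massage from these.

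**Working it through.** **Inputs from the article.** 60 per randomised arm (Abstract, Methods; section 2.8); significance level 5% (section 2.11.6).

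**Inputs assumed, because the article does not give them.** Two-sided testing; 80% power; equal SD (set to 1) before and after; no dropout; baseline-to-follow-up correlation ρ of 0.3, 0.5 or 0.7. The article gives no effect size, SD or power for its 60 per arm, so there is no stated calculation to reproduce.

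**Step 1, post-treatment values only.** The two-sample t-test with 60 per arm detects 0.5157 SD at 80% power. As a check, the normal approximation gives (1.960 + 0.842) × √(2/60) = 2.802 × 0.1826 = 0.511 SD.

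**Step 2, change scores.** The SD is multiplied by √(2(1 − ρ)):
- ρ = 0.3: 0.5157 × √1.4 = 0.610
- ρ = 0.5: 0.5157 × √1.0 = 0.516
- ρ = 0.7: 0.5157 × √0.6 = 0.399

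**Step 3, ANCOVA on baseline.** The SD is multiplied by √(1 − ρ²), ignoring the one degree of freedom spent on the covariate:
- ρ = 0.3: 0.5157 × √0.91 = 0.492
- ρ = 0.5: 0.5157 × √0.75 = 0.447
- ρ = 0.7: 0.5157 × √0.51 = 0.368

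**Step 4, the gain in children.** Against post-only the ratio of variances is 1/(1 − ρ²): 1/0.91 = 1.10, 1/0.75 = 1.33, 1/0.51 = 1.96. Against change scores it is 2(1 − ρ)/(1 − ρ²): 1.4/0.91 = 1.54, 1.0/0.75 = 1.33, 0.6/0.51 = 1.18.

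| Assumed ρ | Post-only (SD) | Change (SD) | ANCOVA (SD) | Gain against post-only | Gain against change |
|---|---|---|---|---|---|
| 0.3 | 0.516 | 0.610 | 0.492 | 10% | 54% |
| 0.5 | 0.516 | 0.516 | 0.447 | 33% | 33% |
| 0.7 | 0.516 | 0.399 | 0.368 | 96% | 18% |

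The two gain columns run in opposite directions. Change scores do worse than post-only values below ρ = 0.5 and better above it, and ANCOVA has the smallest detectable difference in every row.

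**Step 5, why within-arm tests should not carry conclusions.** This is an illustration of a possible reading, not of a planned test. Suppose both arms truly improve by the same 0.3 SD (assumed). Each before/after test has standard error √(2(1 − ρ)/60), that is 0.153, 0.129 or 0.100, and power p of 0.502, 0.642 or 0.851. The chance that exactly one arm is significant is 2p(1 − p): 50%, 46% or 25%, although the arms do not differ.

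**The case against.** The strongest reply is that section 2.11.6 names tests but not the variable tested. An ANOVA or rank sum test on each child's change does use the baseline and does handle the pairing, and the Abstract's wording is compatible with that. This stands in part. A reader might infer that baseline values are discarded, but the article does not say so, and the 10%, 33% and 96% gains apply only if they are. It does not remove the point, because change scores are also less precise than ANCOVA at each correlation considered.

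A second reply is that covariate adjustment is often left to an analysis plan or full protocol that is not shown. That would excuse silence. Here, however, the article states which test applies to each kind of data, and the comment is on that choice.

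Further objections stand as limits:
- The correlation is assumed. Section 5 says many factors affect flora, diet above all, so a low value is plausible for flora summaries. At 0.3 the gain against post-only is only 10%.
- Flora structure is multivariate, so these figures do not apply to it as a whole.
- A reader might infer that within-arm significance tests are planned. No paired or signed-rank test is named; the risk comes from ambiguous wording.
- Before-and-after timing appears in the Abstract but not in section 2.11. The schedule is in Supplementary Material 1, which is not shown.

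**Conclusion.** The point holds as a matter of efficiency and clarity. It would be too strong to call the planned comparison biased or invalid: an unadjusted comparison of randomised arms is valid on final values or on changes. What the article supports is that the stated tests include no baseline covariate, that the analysed variable is not named, and that precision is given up whichever of the two was meant.

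For correlations from 0.3 to 0.7 the loss is equivalent to 10% to 96% more children if final values are analysed, and 54% to 18% if changes are. The size rests on the assumed correlation, equal SDs, 80% power and two-sided 5%. It applies to short chain fatty acids, trace elements, hemoglobin, D-xylose excretion, the gastric measures and scalar summaries of flora. The warning about within-arm conclusions is an inference from the Abstract's wording.

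**What to change.** In section 2.11.6, for each continuous scalar outcome, make the main analysis an ANCOVA restricted to the two randomised arms: post-treatment value (transformed if skewed) on arm and baseline value. Age may be added as an optional covariate. Report the adjusted massage-minus-tablet difference with its 95% confidence interval.

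Add one sentence saying that within-arm changes are descriptive and that conclusions rest on the between-arm contrast. Keep the healthy children as a separate, non-randomised reference.

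The cost is wording only. Baseline values are already planned, and age is already needed for eligibility (section 2.3). No visits, samples or children are added.

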**Results::**

We will review the clinical trial registry in China (http://www.chictr.org.cn/searchprojen.aspx), peer-reviewed journals and academic conferences.

**Conclusion::**

This study will verify the intervention mechanism(s) of pediatric massage on intestinal flora and host metabolism in children with anorexia.

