## Introduction

1

Feeding disorders fall into 3 categories under the Chatoor criteria:^[1]^

(1)feeding disorders of state regulation;(2)feeding disorders of reciprocity; and(3)pediatric anorexia (PN).

PN refers to children with a sustained loss of appetite, who eat less and/or dislike eating. As a disorder of chronic hunger, PN is common in children, with a prevalence of 5% to 10%.^[2]^ The disease is most common in children aged 1 to 5 years.^[3]^ If left untreated, PN can result in childhood malnutrition, body wasting, rickets, anemia, and a decline in immune function, all adverse consequences that can affect growth and development both physically and intellectually, in addition to mental illness.^[4–5]^ In modern medicine, the main treatment for PN is drug treatment, including the use of supplementary trace elements to enhance peptin levels and gastric dynamics^[6]^ However, it is often difficult to determine the exact cause of anorexia in children.^[7]^ Due to the poor compliance of children on oral drugs and the high occurrence of side effects,^[8]^ their clinical application is limited.

As a painless and non-drug therapy, infantile massage is widely applicable to the pediatric disease spectrum, with the advantages of simple operation and a comfortable experience. In clinical practice, massage represents a dominant therapy for PN. Through many years of clinical practice, it has been shown that children with anorexia who receive massage therapy not only significantly improve their appetite, but relieve sallow complexion, abdominal distension, and other accompanying symptoms. Modern medical studies have shown that massage therapy can increase vagus nerve activity and promote appetite regulatory factors, thus increasing gastrointestinal peristalsis^[9]^ and improving digestive function. Massage intervention also correlates with improves the correlation between the brain and intestine axis, intestinal flora activity, and the regulation of host metabolism.

In this study, we explore the biological mechanism(s) of anorexia from the perspective of intestinal flora and the regulation of host metabolism. We further reveal the action site and therapeutic mechanism(s) of pediatric massage for the treatment of anorexia. This furthers our understanding of the optimal treatment methods for the treatment of PN in the clinic.

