### Inclusion criteria

2.3

All subjects will be required to meet the known diagnostic criteria for anorexia in children.^[1]^ The criteria include

(1)a refusal to eat adequate amounts of food for at least 1 month;(2)a failure to communicate hunger and a lack of interest in food;(3)significant growth deficiency;(4)a refusal to eat that is unrelated to an underlying medical illness or a traumatic event;(5)aged 2 to 12;(6)agree to receive massage therapy;(7)consent to the study either directly or through a legal guardian.

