#### Blank group

2.7.2

No interventions will be performed.

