### Randomized grouping

2.8

A total of 60 healthy children will be randomly selected for physical examinations. A statistical expert not involved in the design of the study will use SPSS 22.0 software to generate a series of random sequences, which will be marked onto a card and placed in a sealed envelope. Each subject will receive an envelope at a time-point consistent with the test conditions. Subjects will be randomly divided based on their number into control or test groups (n = 60 per group). For each child, the chiropractor will open the envelope to obtain the grouping code.

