### Single-Blinding

2.9

The massage doctor will have no prior knowledge of the grouping information or treatment regimen contained in the envelope. All participants and relevant health care personnel will not interfere with the study. The evaluator will not be aware of the treatment protocol received by each subject and instructed family members will be asked to complete all relevant study scales. Statisticians will be blinded during all statistical analysis.

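### The trial can estimate a massage-versus-tablet difference in gut and laboratory markers; it cannot verify how massage works in anorexia, as the abstract says it will

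*Protocol article*

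**What the plan says.** **The claim.** The abstract's Conclusion reads: "This study will verify the intervention mechanism(s) of pediatric massage on intestinal flora and host metabolism in children with anorexia". The Introduction (section 1) first states a softer aim, "we explore the biological mechanism(s) of anorexia from the perspective of intestinal flora and the regulation of host metabolism", and then says the study will reveal where massage acts and by what therapeutic mechanism. Section 4 adds that the assays put that mechanism on an objective footing.

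**The randomised contrast.** The abstract's Methods state that "subjects will be randomly assigned to either the massage or control group (n = 60 per group"), and section 2.8 agrees: "Subjects will be randomly divided based on their number into control or test groups (n = 60 per group"). The comparator is active: "The control group will be administered oral Jianweixiaoshi tablets over 4 weeks". Section 5 describes the tablet's efficacy as established.

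**The third group.** For the blank group, section 2.7.2 says "No interventions will be performed". Section 2.8 speaks of 60 healthy children chosen for examination. The article never says outright that these are the blank group, but no other reading fits. On any reading, the group is not part of the randomisation.

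**The outcomes.** Sections 2.11.1 to 2.11.3 list intestinal flora and fecal SCFAs as main outcomes. The secondary outcomes are Zn, Fe, Ca, hemoglobin, urinary D-xylose excretion, and gastric emptying and motility. The abstract gives the same set. Section 2.3 requires "significant growth deficiency" at entry, and section 2.9 says "instructed family members will be asked to complete all relevant study scales" without naming a scale.

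**The concern.** A claim to have verified how massage works in anorexia needs two things.

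1. A contrast that isolates what massage does, compared with what would have happened without it.
2. A measurement of the clinical state that the mechanism is supposed to improve.

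The article provides neither. The one randomised comparison is against a treatment that the authors believe works, and no listed outcome records appetite, intake or growth.

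What is at stake is the conclusion that can be printed. If the plan is followed as written, a significant flora difference invites the statement that massage treats anorexia through the flora. A non-significant one invites the statement that massage has no effect on flora, or the same effect as the tablet. None of these would follow from the data.

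**Working it through.** **Step 1: what the randomised difference estimates.** Let M and T be the mean change in a marker under massage and under tablets. Let U be the mean change that the same children would have shown untreated. Then

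M − T = (M − U) − (T − U) = massage effect − tablet effect.

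The trial observes M and T in randomised groups but not U. One observed difference cannot fix two unknown effects.

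**Step 2: whether other data in the trial supply U.**

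- *Healthy children.* They show what happens to children without the disease. They can serve as a reference for a normal profile, but they do not show the four-week course of untreated anorexia.
- *Before-after change within the massage arm.* This equals the massage effect plus U. U contains the passage of time, regression to the mean (children enter because they are eating poorly and growing poorly) and diet. Section 5 admits that dietary influence on the flora is hard to exclude and says that dietary and water guidance will be given.

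**Step 3: whether the tablet effect can be taken as zero.** The article does not say that the tablet changes flora. However, section 5 treats the tablet as effective and also says that flora respond to diet. A tablet that makes children eat more could therefore move the main outcome. Zero is an assumption that the article neither states nor supports.

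**Step 4: what this does to a null result (illustration only).** The article gives no effect size, SD or power, so there is no stated figure to reproduce.

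Assumptions: massage effect 0.6 SD versus no treatment; tablet sharing a fraction f of it; 60 analysed per arm; two-sided 5% (the plan states P < .05 without sidedness); normal approximation.

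- Standard error in SD units: √(2/60) = 0.183.
- Power = Φ(d/0.183 − 1.96) + Φ(−d/0.183 − 1.96), with d = 0.6 × (1 − f).

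| f | d (SD) | Power |
|---|---|---|
| 0 | 0.60 | 91% |
| 0.25 | 0.45 | 69% |
| 0.50 | 0.30 | 38% |
| 0.75 | 0.15 | 13% |
| 1 | 0 | 5% (alpha only) |

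The smallest difference detectable with 80% power is (1.96 + 0.84) × 0.183 = 0.51 SD. In every row massage has the same real effect. Only the unknown tablet effect varies, and power runs from 91% down to the false-positive rate.

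**Step 5: disease definition and outcomes side by side.**

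| What defines the disease | Listed as an outcome? |
|---|---|
| Appetite, interest in food (sections 1, 2.3) | No |
| Amount eaten (sections 1, 2.3) | No |
| Growth (section 2.3) | No |

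The Discussion's causal account runs from disturbed flora and SCFAs, through hormones, to lost appetite. The trial measures the start of that chain and, as listed, not its end. Because flora also respond to diet, a flora change could be a consequence of eating more rather than its cause. The listed outcomes cannot tell these apart.

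**The case against.** **The anchor sentence is narrow, and the aim is elsewhere called exploratory.** Read strictly, the abstract's Conclusion concerns massage acting on flora and metabolism, which the main outcomes do measure. This stands in part: much of the remedy is a change of wording that brings the Conclusion into line with the softer Introduction aim. It does not remove the problem, because sections 1 and 4 use the broader therapeutic language, and even the narrow sentence asserts an effect of massage itself.

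**A reader might infer that a significant difference could not be attributed to massage at all.** That goes too far. A randomised difference is causally attributable to receiving massage instead of tablets. What it cannot give is the effect of massage compared with no treatment.

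**The active comparator is a declared choice.** Section 5 discusses it openly. The point is not that a sham or untreated arm must be added, but that the conclusion should match the comparator chosen.

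**A reader might infer that an appetite scale is already being collected.** Section 2.9 names no scale and does not say what any of them measures, so this cannot be assumed. The evaluation schedule is in a supplement that is not shown and may name them. The outcome list, however, appears twice and is the same both times, with no scale in it.

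**A reader might infer that the single-blind paragraph is false because families know the treatment.** Section 2.9 claims blinding of the evaluator and the statisticians, not of families. No listed outcome is parent-rated. Unblinded rating would matter only if a family-completed scale became an outcome.

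**A reader might fault the plan for lacking a formal analysis that links flora change to clinical change.** That is ordinary analysis-plan content. Its absence from a protocol article is not an error.

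**Conclusion.** The point holds in this form: the stated conclusion claims more than the design can deliver. The trial can validly estimate the randomised massage-versus-tablet difference in flora, SCFAs and the secondary markers, with healthy children as a non-randomised reference. It cannot isolate the effect of massage, cannot read a non-significant difference as no effect or equal effect, and cannot tie marker changes to improvement in anorexia on the outcomes listed.

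The problem is one of inference, and no stated number is wrong. The fall in power from 91% to 5% depends on an assumed 0.6 SD effect and an unknown shared fraction. It shows how little a null result would say and does not forecast the trial's result. The conclusion rests on the blank group being outside the randomisation, which the article states, and on its being the healthy children, which is inferred. It should be corrected before the results are reported.

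**What to change.** 1. **Reword the aim and conclusion** (abstract, and sections 1 and 4 where they speak of therapeutic mechanism). Suggested text: *This exploratory study will estimate the difference between massage and Jianweixiaoshi tablets in intestinal flora, fecal SCFAs and the listed secondary measures in children with anorexia, with healthy children as a non-randomised reference. A non-significant difference will not be taken as evidence of equal effect or of no effect.*
2. **Add change in weight and height z-scores as secondary outcomes.** Growth already has to be assessed to judge the entry criterion, so only the repeat measurement is new.
3. **Say what the family-completed scales in section 2.9 are.** If any measures appetite or intake, list it as a secondary outcome and flag it as unblinded. If none does, keep statements about appetite out of the conclusion.
4. **Report any link between marker change and clinical change as association only.**

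Cost: a more modest headline claim and one repeat weight and height per child. The arms, the sample size and the treatments stay as they are.
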